# Treatment of fatigue with physical activity and behavioural change support in vasculitis: study protocol for an open-label randomised controlled feasibility study

**DOI:** 10.1136/bmjopen-2018-023769

**Published:** 2018-10-30

**Keywords:** vasculitis, fatigue, exercise, ANCA, self-management

## Abstract

**Introduction:**

Fatigue is a major cause of morbidity, limiting quality of life, in patients with antineutrophil cytoplasmic antibody-associated vasculitis (AAV). The aetiology of fatigue is multifactorial; biological and psychosocial mediators, such as sleep deprivation, pain and anxiety and depression, are important and may be improved by increasing physical activity. Current self-management advice is based on expert opinion and is poorly adhered to. This study aims to investigate the feasibility of increasing physical activity using a programme of direct contact and telephone support, to provide patient education, encourage behaviour self-monitoring and the development of an individual change plan with defined goals and feedback to treat fatigue compared with standard of care to inform the design of a large randomised controlled trial to test the efficacy and cost effectiveness of this programme.

**Methods and analysis:**

Patients with AAV and significant levels of fatigue (patient self-report using multidimensional fatigue index score questionnaire ≥14) will be randomised in a 1:1 ratio to the physical activity programme supported by behavioural change techniques or standard of care. The intervention programme will consist of 8 visits of supervised activity sessions and 12 telephone support calls over 12 weeks with the aim of increasing physical activity to the level advised by government guidelines. Assessment visits will be performed at baseline, 12, 24 and 52 weeks. The study will assess the feasibility of recruitment, retention, the acceptability, adherence and safety of the intervention, and collect data on various assessment tools to inform the design of a large definitive trial. A nested qualitative study will explore patient experience of the trial through focus groups or interviews.

**Ethics and dissemination:**

All required ethical and regulatory approvals have been obtained. Findings will be disseminated through conference presentations, patient networks and academic publications.

**Trial registration number:**

ISRCTN11929227.

Strengths and limitations of this studyFatigue is a major cause of poor quality of life in patients with antineutrophil cytoplasmic antibody-associated vasculitis (AAV) and has no evidence base to direct treatment.This study will provide the evidence required to design a large randomised controlled trial to address whether physical activity improves fatigue in patients with AAV.The study is limited by its size; as a feasibility study, it has a small sample size and will not provide evidence of efficacy but will provide estimates to calculate sample size for a larger study

## Introduction

Fatigue is a common symptom limiting quality of life in patients with a wide range of inflammatory and other chronic diseases including systemic vasculitis.^1^ Ninety-two per cent of patients with antineutrophil cytoplasmic antibody (ANCA)-associated vasculitis (AAV) consider fatigue as the most important symptom affecting their well-being,^1 2^ and it has been causally linked to reduced social participation, social withdrawal and unemployment.^3 4^ Despite the significance of the problem, there are currently no recommended therapies specifically for fatigue in patients with AAV. Current self-management advice provided by the National Institute for Health and Care Excellence (https://cks.nice.org.uk/tirednessfatigue-in-adults#!scenariorecommendation:1) and Arthritis Research UK (ARUK) (https://www.arthritisresearchuk.org/arthritis-information/daily-life/fatigue.aspx) is based on expert opinion and pragmatic advice without any underpinning evidence base. This is therefore, a major area of unmet need and has been identified as a priority research area by patients and ARUK.

The aetiology of fatigue is multifactorial^5 6^ and related to a number of interacting central (such as reduced motivation and increased perception of effort) and peripheral (impaired muscle or cardiovascular function) biological and psychosocial mediators including sleep deprivation, pain, depression, lack of physical activity and reduced cardiovascular fitness, similar to other chronic diseases.^7–10^ Only 47% of patients with AAV participate in at least 1 hour of moderate or vigorous physical activity per week (unpublished audit of 100 patients), and patients are reluctant to increase physical activity often due to fatigue, or for fear of worsening their fatigue.^11^ Both central and peripheral components of fatigue need to be addressed in any successful treatment intervention.

Physical activity interventions improve sleep, quality of life, anxiety and depression in patients with chronic diseases and have been shown to improve fatigue in the short term.^12^ However, studies with long-term follow-up often report no sustained increase in physical activity once support is discontinued.^13^ The addition of cognitive behavioural support (CBS), as commonly implemented in successful chronic disease self-management programmes,^14^ to a physical activity intervention may result in improved self-efficacy and a sustained increase in physical activity once the formal programme is completed.^15–18^

Our programme, using direct contact and telephone support, will provide patient education, encourage behaviour self-monitoring and the development of an individual change plan with defined goals and feedback to increase physical activity. These interventions have not been investigated to treat fatigue in patients with systemic vasculitis. A pilot study of five patients with AAV with fatigue suggested physical activity, supported by behavioural intervention, was an acceptable approach for patients with AAV and fatigue.^19^

## Aims and objectives

The aim of this study is to assess the feasibility and acceptability of undertaking a phase III randomised controlled trial (RCT) of physical activity with behaviour change support including device assisted self-monitoring and telephone support with cognitive behavioural strategies compared with standard of care in patients with AAV.

The specific objectives of the study are to:Assess different recruitment methods to the trial for example, where and how patients are identified and recruited.Assess recruitment and retention rates in the trial.Assess the acceptability of the intervention and the burden of trial participation on patients.Assess adherence to the trial intervention.Assess the safety of the intervention with respect to possible injury and deterioration in fatigue levels as a result of participating in a physical activity trial.Assess the effect of trial participation on activity levels in patients in the standard care group.Test procedures for the trial, including delivery of the standardised protocolled intervention and administration of trial questionnaires and other outcome measurement tools, and identify areas that may improve the design and implementation of the intervention.Collect data on the variability of the outcome measures to inform a power calculation for a definitive trial.Provide an estimate of the cost of implementing the intervention.Collect feedback from patients on their experience of participating in the study.

## Methods

### Overview of study design

This is a single centre, open-label randomised controlled feasibility study with a nested qualitative component. Feasibility will be determined by assessing recruitment, adherence to the intervention and retention rates. Acceptability and patient experience will be assessed through patient-reported outcome (PRO) questionnaires, and an optional nested qualitative study consisting of either focus groups or semistructured telephone interviews if insufficient numbers can be recruited to form focus groups.

Fifty participants will be randomised (via a computer-generated programme) in a 1:1 ratio to the intervention or standard care for this population (figure 1 study flow). The randomisation will be minimised by age (<65 vs ≥65 years). Participants randomised to the intervention arm will complete eight supervised (one per week) and 12 telephone coaching sessions over 12 weeks. Outcomes will be assessed at baseline, 12, 24 and 52 weeks from the first exercise session for those in the intervention group and from randomisation for those in the standard care group.

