### Intervention group

The intervention is a physical activity and behavioural change support programme, plus standard care. The physical activity intervention will provide support for 12 weeks; weeks 1–8 will consist of weekly (where possible) direct contact in groups of 4–7 patients and additional individual telephone health coaching once weekly (where possible), then in weeks 9–12, telephone health coaching only will be provided. The intervention will be staged adapted, and participants will be encouraged to increase physical activity within their capabilities. Participants will be provided with personal activity self-monitoring devices, which are wrist-worn accelerometers (Fitbit Model FB405BKL), providing individual feedback on daily physical activity. The supervised activity sessions will incorporate CBS (eg, goal setting, finding social support and understanding the costs/benefits of exercise etc) to promote long-term participation in physical activity. The intervention includes education, monitoring and assessment of progress and teaches skills to improve self-efficacy.

Individual specific, measurable, achievable, realistic and timed (SMART) goals^24^ will be set by the participants with guidance from the intervention facilitator and will focus on increasing activity levels. The behavioural goal is for participants to achieve at least 30 min of moderate intensity activity, 5 days per week, ideally in bouts of 10 min, as per UK government recommendations, although any increase in physical activity or reduction in sedentary time will be viewed positively. The Fitbit activity self-monitor is supported with online web interfaces that facilitate effective components of physical activity interventions (https://www.fitbit.com/login).^25^

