### Study procedures

The study outcomes, measurement methods and assessments are summarised in table 1. Data are collected at baseline, and then at 12, 24 and 52 weeks, from the first exercise session for those in the intervention group and from randomisation for those in the standard care group. Data on recruitment, number of activity sessions and telephone coaching sessions completed and drop outs will also be recorded.

**Table 1 T1:** Visit overview

Visit	Prebaseline	Baseline	Baseline (+4 weeks)	Weeks 1–8	Weeks 9–12	Week 12*	Week 24*	†Week 52*
Identification of eligible patients	x							
Eligibility check	x	x						
Valid informed consent		x						
Relevant medical history taken		x						
Randomisation (without patient present)			x					
Activity advice telephone call (control arm only)‡				x				
Exercise visits (intervention arm only)				x				
Weekly telephone coaching contacts (intervention arm only)				x	x			
Follow-up clinic visits*§						x	x	
Final assessment (postal questionnaires)*§								x
Quality of life questionnaires		x				x	x	x
Focus groups or interviews (postintervention)					x	x	x	

*The timing of the follow-up visits for intervention group are taken from intervention start date, not randomisation date; for the control group, the timing is taken from randomisation date.

†52 weeks follow-up assessment can be completed—2 weeks before due date and up to 8 weeks after the due date.

‡Control group have one telephone call in week 1 (postrandomisation) to receive standard activity advice only.

§12-week and 24-week follow-up assessments can be completed up to—2 weeks before due date and up to 3 weeks after the due date.

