The primary analysis to assess the stop-go criteria will be undertaken once all participants have completed the 24-week assessment, and corresponding outcome data has been entered onto the study database and validated as being ready for analysis. Feasibility outcomes including the three components of the stop-go criteria will be analysed by pooling the two randomised groups and presenting overall estimates with 95% CI. Reasons for non-entry into the trial will be assessed, particularly in relation to the patient eligibility criteria and reasons for patient refusal. Data on patients who stop the intervention and/or who do not complete the trial (such as withdrawals and those lost to follow-up) will be collected throughout the trial to allow assessment of patient adherence and retention rates. Reasons for non-adherence and non-completion will be analysed descriptively.

All clinical and patient-reported outcomes will primarily take the form of simple descriptive statistics (eg, proportions and percentages, means and SD) and where appropriate, point estimates of effects sizes (eg, mean differences and relative risks) and associated 95% CI. Data return rates at each time point will be assessed along with data completeness of the various outcomes measures. This will inform the use of appropriate questionnaires for the primary outcome in a future study. The data will be analysed using the intention to treat principle, where patients are analysed in the treatment group to which they were randomised regardless of adherence to intervention or compliance with the protocol.

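### The follow-up clock starts at randomisation for controls but at first attendance for the intervention arm, so any start delay lengthens follow-up in one arm only and never-starters have no due date

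*Protocol article*

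**What the plan says.** Overview of study design gives the schedule, "Outcomes will be assessed at baseline, 12, 24 and 52 weeks", and counts it "from the first exercise session for those in the intervention group and from randomisation for those in the standard care group". Study procedures repeats the rule, and the first footnote to Table 1 makes clear that it is deliberate: "The timing of the follow-up visits for intervention group are taken from intervention start date, not randomisation date". The same footnote has control visits counted from randomisation. The visit windows are set around these due dates. For weeks 12 and 24, "12-week and 24-week follow-up assessments can be completed up to—2 weeks before due date and up to 3 weeks after the due date"; for week 52, "52 weeks follow-up assessment can be completed—2 weeks before due date and up to 8 weeks after the due date". Table 1 puts randomisation in a column labelled four weeks after baseline, for both arms.

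The Intervention group section describes weekly "direct contact in groups of 4–7 patients". The article gives no maximum interval from randomisation to the first session and no substitute date for a patient who attends none.

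Study outcomes and data analysis plans mainly descriptive summaries, with mean differences, relative risks and 95% confidence intervals where appropriate. Under its intention-to-treat principle, "patients are analysed in the treatment group to which they were randomised regardless of adherence to intervention". The primary analysis waits until every participant has completed the 24-week assessment.

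**The concern.** Randomisation makes the arms comparable from the moment of allocation. Here one arm keeps that origin, while the other takes an origin that occurs later and depends on what happens after allocation. Two consequences follow from the rule itself.

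First, at a visit with the same label, intervention patients have had more time since baseline and since randomisation than controls, by whatever their start delay was. Fatigue, activity and quality-of-life scores are then compared at different elapsed times. Injury, relapse and cardiovascular events, which are self-reported at 12 and 24 weeks, may be counted over unequal time at risk.

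Second, a patient allocated to the programme who never attends has no first-session date, so the rule yields no 12-, 24- or 52-week due date. A control patient always has one. Missing outcomes from this source can arise in one arm only, and among patients unlikely to resemble the rest of the arm.

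The study is not powered for efficacy, so no formal test is at stake. Testing trial procedures, assessing safety and collecting outcome variability for a definitive trial are stated objectives, however, and a green result means proceeding with the protocol essentially unchanged. The timing rule could therefore carry over into the full trial.

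**Working it through.** The plan gives no figure to reproduce here. The check is arithmetic on the timing rule.

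**Inputs from the article.** Nominal visits v = 12, 24 and 52 weeks. Windows are −2 to +3 weeks (weeks 12 and 24) and −2 to +8 weeks (week 52). Fifty patients at 1:1 make 25 per arm.

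**Assumed input.** The mean delay d from randomisation to first session is not stated; d = 0, 2 and 4 weeks are shown.

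**Time from randomisation to visit.** Control: v. Intervention: v + d. Relative excess: d / v.

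| Visit | Control | d = 0 | d = 2 | d = 4 |
|---|---|---|---|---|
| 12 | 12 | 12 (0%) | 14 (2/12 = 17%) | 16 (4/12 = 33%) |
| 24 | 24 | 24 (0%) | 26 (2/24 = 8%) | 28 (4/24 = 17%) |
| 52 | 52 | 52 (0%) | 54 (2/52 = 4%) | 56 (4/52 = 8%) |

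**Windows, in weeks from randomisation.** Control: 10–15, 22–27 and 50–60. Intervention at d = 2: 12–17, 24–29 and 52–62, overlapping the control windows by 3, 3 and 8 weeks. Intervention at d = 4: 14–19, 26–31 and 54–64, overlapping by 1, 1 and 6 weeks.

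**Time since baseline.** A baseline-to-randomisation lag b is common to both arms, so the gap is (b + v + d) − (b + v) = d weeks whatever b is. The percentage is smaller: with b = 4 and d = 4, the week-12 visit falls at 20 weeks against 16, which is 25% later.

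**Event comparisons.** If events are rare, occur at a constant rate and are counted from randomisation, a relative risk with no true effect would read about (24 + d)/24 at the 24-week visit: 1.08 for d = 2 and 1.17 for d = 4. The article does not state the recall period for self-reported events, so this is conditional.

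**Never-starters.** Their number is unknown. If 1 to 4 of 25 never attended (assumption), 1/25 = 4% to 4/25 = 16% of the intervention arm would have no due date, against none in the control arm. This part does not depend on d.

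**The case against.** The rule has a reason: counting from the first session places the week-12 assessment at the end of the 12-week programme. The article disclaims efficacy inference and makes estimates of effect secondary to description. With about 25 patients per arm, a shift in a relative risk to 1.08 or 1.17 would be small beside its confidence interval. The visit windows already allow a 5-week spread in both arms at weeks 12 and 24. All of this stands and limits the consequence. It does not remove the asymmetry: the windows apply equally to both arms, while the start delay is added to one.

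Three stronger readings are tempting, and the article does not support them.

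- A reader might infer from the group format that early recruits must wait until a group fills. The article does not say that groups are closed or must be full before anyone starts. Rolling entry fits the text equally well, and Table 1 lists the exercise visits and the control arm's week-1 call in the same column. Some wait is plausible, but its existence and length are not documented.
- A reader might infer that the rule contradicts intention to treat. It moves nobody between groups and excludes nobody from analysis. It leaves the follow-up dates of never-starters undefined, which is a narrower fault. The full protocol may hold a fallback date; the rule as published supplies none.
- A reader might infer that the drop-out criterion is distorted, or that losses before the first session go uncounted. Drop-out is defined as complete withdrawal with no start clock, is pooled over both arms, and is collected throughout the trial. Nothing excludes a withdrawal between randomisation and the first session. Recruitment and adherence are likewise not defined by the visit clock.

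**Conclusion.** The point holds as a one-sided timing rule that is easily repaired. That follow-up is longer in one arm by the start delay, and that a never-starter has no due date, both follow directly from the text. The size depends on an unstated delay: nil if sessions begin at randomisation; at an assumed mean of 2 or 4 weeks, 17% or 33% more time to the week-12 visit and 8% or 17% more to the week-24 visit. What is affected is the descriptive between-arm estimates, the safety comparisons and data return from never-starters. The stop-go rates are unaffected as defined. The only link to that decision is practical: its analysis waits for all 24-week assessments, and a never-starter has no date for one. No sample size or power figure changes.

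**What to change.** At randomisation, give every patient in both arms a nominal start date by the same rule, for example the next planned group start. Count 12, 24 and 52 weeks from that date whether or not the patient attends, and keep the existing windows around it. Both arms then share the same nominal visit times and the gap due to the rule is zero. Every randomised patient has due dates, and week 12 stays close to the end of the programme for those who start on time. In the report, tabulate actual days from baseline and from randomisation to each assessment, by arm.

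The cost is a small scheduling amendment with no change to sample size. Control visits move slightly later, and a patient who starts late may be assessed before finishing the programme. Randomising in cohorts is optional and not needed for this fix.

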**Figure 1 F1:**
[figure not shown]
Consort diagram.

### Sample size

This is a feasibility study, and therefore a formal sample size calculation has not been performed. The study is not designed or powered to detect a statistically significant difference in efficacy between the two treatment arms.

A pragmatic recruitment target of 50 participants has been chosen as we expect this number will be feasible within a single centre with a population of 250 patients and should be sufficient to provide estimates of the feasibility outcomes. A sample size of between 24 and 50 is recommended for pilot studies to estimate sample sizes for a full trial.^20^

### Participants and recruitment

Patients will be recruited to the study via the dedicated vasculitis service at University Hospitals Birmingham NHS Foundation Trust (UHB NHSFT) or via response to study adverts placed in the Vasculitis UK newsletter or other hospital clinics. Confirmation of eligibility for the study will be with the patient’s own clinician. Patients are eligible if they are 18 years of age or older, have a diagnosis of AAV as classified by the European Medicines Agency Algorithm,^21^ have been in remission for at least 6 months on the day of consent (defined by Birmingham Vasculitis Activity Score Version 3 (BVASv3)^22^=0 on day of consent and prednisolone dose <7.5 mg for 6 months) and have significant fatigue levels (multidimensional fatigue inventory (MFI)-20 general fatigue score ≥14). Exclusion criteria include inability to provide informed consent, inability or unwillingness to undertake physical activity, comorbidities considered by their own clinician to contraindicate an increase in physical activity and an inability to understand and complete questionnaires.

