### Study outcomes and data analysis

The primary outcome of this feasibility trial is to determine if a full RCT comparing physical activity with behaviour change support versus standard care in patients with AAV is feasible. This decision will be made using a composite assessment of both quantitative and qualitative data based on a traffic light system using predefined stop-go criteria. The three criteria contributing to the traffic light system include^1^ recruitment rates, defined as the proportion of eligible patients recruited into the study^2^; successful adherence to the intervention, defined as attendance at a minimum of 4 of the 8 visits for the face to face support, and acceptance of a minimum of 3 of the 4 telephone support calls in weeks 9–12 and^3^ study drop-out, defined as complete withdrawal from the study, with no further data collected from the participant. The traffic light system comprises (1) green light: recruitment rate >50%; adherence rate >75% and drop-out rate <15% excluding those patients who drop-out or are unable to achieve adherence due to disease activity. If all three criteria are met, we will proceed to a full trial with the protocol unchanged (unless there is a clear message from the qualitative work that would improve the protocol). (2) Amber light: recruitment rate 30%–50%, adherence rate 50%–75% or drop-out rate 15%–30% excluding those patients who drop-out or are unable to achieve adherence due to disease activity. If one or more of our amber light criteria are met, we will adapt the protocol in light of the result of the feedback from the qualitative work and our experience to improve whichever criteria are not at the ‘green-light’ level before proceeding to full trial if possible. We will assess whether adaption of the protocol will require a further feasibility study or pilot study before progressing. (3) Red light: recruitment rate <30%, adherence rate <50% or drop-out rate >30% excluding those patients who drop-out or are unable to achieve adherence for disease activity. If one or more of these criteria are met we would consider the current protocol not feasible and not progress to a full RCT.

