### Nested qualitative study

Focus groups of 4–6 participants will be carried out to discuss their experience of the trial. Two groups will consist of people who participated in the trial and participated in the intervention, one group of people who participated and received standard of care and the final group will be made up of people who did not wish to participate in the trial. Individuals who did not wish to participate in the trial will be contacted and invited to participate in a focus group to better understand the reasons for non-participation. If we cannot form one or more of the focus groups described, then patients will be invited to participate in 1:1 semistructured telephone interviews. The qualitative phase will be conducted by a researcher not involved with the rest of the study and will collect data on the experiences of the study and the intervention, in more detail, and to gather suggestions for improvements to the design of a future RCT.

Focus groups and interviews will be recorded and transcribed verbatim. QSR NVivo 8 will be used for data management and data analysed using a framework approach,^35^ facilitated by the use of to identify freely emerging themes and categories. Those who did not participate in the trial will be invited to complete the same questionnaires as collected during the trial. These will be analysed as above using simple descriptive statistics.

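### Unwillingness to exercise is an exclusion criterion, so the stop-go recruitment rate can omit patients who decline for that reason, or depend on how they are logged

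*Protocol article*

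**What the plan says.** Two definitions in the protocol article meet here.

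- **Eligibility** (Participants and recruitment): "Exclusion criteria include inability to provide informed consent, inability or unwillingness to undertake physical activity". Comorbidities that the patient's own clinician considers a contraindication are listed separately.
- **Recruitment criterion** (Study outcomes and data analysis): "recruitment rates, defined as the proportion of eligible patients recruited into the study". The bands, in per cent, are "green light: recruitment rate >50", "Amber light: recruitment rate 30%–50" and "Red light: recruitment rate <30". Recruitment is one of three stop-go criteria, with adherence and drop-out. Green needs all three; one red is enough to stop.

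Three other places bear on the point.

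- The Introduction says of this population that "patients are reluctant to increase physical activity often due to fatigue, or for fear of worsening their fatigue".
- Study outcomes and data analysis says that reasons for non-entry will be examined, and distinguishes eligibility criteria from patient refusal.
- Nested qualitative study plans several focus groups, and "the final group will be made up of people who did not wish to participate in the trial".

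The only patients set aside within the traffic-light rule are those who drop out or cannot adhere because of disease activity. Nothing in the article returns patients excluded for unwillingness to the recruitment denominator.

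**The concern.** Physical activity is the intervention. Being unwilling to undertake it is a way of declining the trial treatment, and differs in kind from a diagnostic, safety or consent criterion. Placing it among the exclusions moves a form of refusal out of the quantity meant to measure acceptance.

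The recruitment rate helps decide whether a full trial goes ahead and whether its protocol changes. If clinically suitable patients who will not exercise are classed as ineligible, the rate describes uptake among those already willing to be active. If some are classed as ineligible and others as refusers, the rate reflects logging practice as well as uptake. Both weaken a component of the primary outcome, and the Introduction gives reason to expect some such patients.

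**Working it through.** **Plan's own figure.** There is none to reproduce. The article gives a recruitment target but no expected rate, no number eligible and no number unwilling.

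**Inputs from the article.** Target of 50 participants and a centre population of 250 (Sample size); rate = recruited / eligible; green above 50%, amber 30% to 50%, red below 30% (Study outcomes and data analysis).

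**Assumed inputs.** E = patients counted as eligible under the text, including being willing. U = patients who meet every other criterion and are excluded only for unwillingness. Both are shown as ranges.

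**Formulas.**
- Rate with the unwilling excluded = 50 / E.
- Rate with the unwilling counted as refusals = 50 / (E + U).
- Ratio of the first to the second = (E + U) / E, which exceeds 1 whenever U > 0. The direction is therefore fixed: exclusion can only raise the rate.

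**Where the bands fall with 50 recruited.**
- Green: denominator of at most 99 (50/99 = 50.5%; 50/100 = 50.0% is amber).
- Amber: 100 to 166 (50/166 = 30.1%).
- Red: 167 or more (50/167 = 29.9%).

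**Results.**

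| E (assumed) | Unwilling excluded | Smallest U that changes the light | Unwilling counted |
|---|---|---|---|
| 80 | 50/80 = 62.5%, green | 20 | 50/100 = 50.0%, amber |
| 90 | 50/90 = 55.6%, green | 10 | 50/100 = 50.0%, amber |
| 95 | 50/95 = 52.6%, green | 5 | 50/100 = 50.0%, amber |
| 120 | 50/120 = 41.7%, amber | 47 | 50/167 = 29.9%, red |

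At E = 90, moving from green all the way to red would take U = 167 − 90 = 77.

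**Sampling error.** The Wilson 95% interval for 50/90 is 45.3% to 65.4%, so the step from 55.6% to 50.0% lies well within chance variation. The difference between the two definitions is nevertheless systematic: more recruitment under the same coding would not remove it.

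**The case against.** The strongest reply is that the text does not force these patients out. The article treats eligibility and refusal as distinct reasons for non-entry, so a clinically suitable patient who is approached and says no can be logged as a refusal. This stands in part: upward bias is possible but not established. It does not remove the point, because the exclusion criterion fits the same patient and the article does not say which category takes precedence.

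Other replies stand and limit the point.

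- **Scope.** The exclusion concerns unwillingness to be physically active. Patients who decline because of travel, weekly visits, group format, telephone calls or randomisation remain eligible and remain in the denominator.
- **Main reason for refusal.** A reader might infer from the Introduction that reluctance to exercise is the main expected reason for refusal. The article reports reluctance, but gives no rate and does not say that these patients would decline a supported programme.
- **Automatic green.** A reader might infer that a raised recruitment rate sends the protocol forward unchanged. Green also needs adherence above 75% and drop-out below 15%, the decision combines quantitative and qualitative evidence, and a clear qualitative message can alter the protocol even under green.
- **Under-recruitment later.** A reader might infer that the full trial would under-recruit. If it kept the same criteria, recruited over eligible would be the matching rate for its own eligible pool. The problem arises only if the rate is applied to a pool that includes unwilling patients.
- **Qualitative gap.** A reader might infer that unwilling patients would miss the non-participant focus group. Its description already covers them, and nothing restricts it to the formally eligible.
- **Plausibility of red.** A denominator of 167 is 167/250 = 66.8% of the centre population, all meeting the remission and fatigue criteria, unless adverts bring in many more.

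Screening-log detail may also sit in the full protocol. The two definitions that conflict, however, are both stated in the article.

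**Conclusion.** The point holds as a flaw in the definition of one stop-go criterion. Read literally, the eligibility text removes clinically suitable patients who do not want to exercise from the recruitment denominator; read more loosely, it leaves their classification to whoever completes the log. The direction of any effect is certain. Its size is unknown, and every percentage above rests on assumed values of E and U.

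The consequence is greatest when the rate is close to a threshold: with 50 recruited and 90 counted as eligible, 10 patients separate green from amber. Far from a threshold, the same number may change nothing. The article does not support the stronger conclusion that the recruitment light is in fact biased to green or that the progression decision would be wrong. This is a worthwhile, inexpensive correction and not a must-fix.

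**What to change.** - State that, for the stop-go recruitment rate, patients who meet all other criteria but are unwilling to undertake physical activity count as eligible and not recruited (refusals).
- Keep inability and clinician-judged contraindication as exclusions.
- Give unwillingness its own code in the screening log, separate from inability. The criterion joins the two, and without separate records the alternative rate could not be reconstructed later.
- Report the rate under both definitions, and say that the light is read from the one that counts unwilling patients as refusals.

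The cost is one sentence on the denominator and one log code, with no extra participants. The downside is a somewhat less favourable recruitment rate.
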